## Introduction

Parkinson’s disease (PD) is a common neurodegenerative disease
^1^ characterised by the death and dysfunction of dopaminergic neurons in the substantia nigra
^2^. PD causes progressive motor symptoms such as problems with gait
^3^ and non-motor symptoms such as visual and cognitive impairment
^1^. Cognitive impairment is common in PD with reports of dementia ranging up to ~80%
^4^, and may occur early in the disease process
^5^. Visual dysfunction is also common in people with PD, with up to 78% of people with PD reporting at least one visual problem
^6^. Gait impairment in PD is complex, involving multi-system dysfunction and has been widely related to cognitive, and to a lesser extent visual deficits. A more robust understanding of these complex processes and their interactions will inform underlying mechanisms of gait impairment in PD, which may provide insight for future therapeutic intervention. Interventions, such as visual cues (prompts; transverse tape lines to step over) are currently used to ameliorate features of gait disturbance in PD resistant to dopaminergic medication, such as festination, hesitation and freezing of gait
^7,
8^. However, visual cue response is selective
^9^ and the mechanisms that contribute to the response are unclear.

To date, associative (correlational) and online manipulation (via dual tasks and environmental changes) studies have investigated the independent contribution of cognition and vision in gait in PD. However, cognitive and visual functions likely interact and have a combined - impact on gait in PD. Recent technological progress has enabled the monitoring of online visuo-cognition through behavioural outcomes such as visual sampling which reflects both visual
^10,
11^ and cognitive
^12–
14^ processes. Visual sampling is the combination of saccadic fast eye-movements and fixations (pauses between saccades on areas of interest) made during real-world activities
^15^. However, research is compromised by several technological limitations which need to be addressed to ensure robust data collection and analysis. For example, there is currently no ‘gold standard’ visual sampling measurement device or outcome measure and there is also a lack of device accuracy or reliability reporting in all previous studies
^15^.

Visual sampling (specifically saccades) allow orientation to the visual environment bringing areas of interest into high visual acuity (foveation or focus)

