^16^. Saccades are impaired in PD and exhibit reduced speed, amplitudes and latencies
^17–
22^. Impaired saccadic eye movements, with reduced latencies and increased error rates have also been reported in PD dementia and dementia with Lewy Bodies, further implicating central neuro-degeneration as a determinant of ocular motor function
^23,
24^. However, the specific contribution of cognitive and/or visual functions to visual sampling during gait in PD and how this impacts gait deficit is currently poorly understood.

Much of the previous saccadic activity research is limited due to the almost exclusive use of static testing protocols (e.g. computerised tasks in sitting)
^18,
25^, which may not be applicable to real-world situations. A recent review of dynamic motor tasks (e.g. gait, obstacle crossing, turning etc.) in PD and older adults
^15^, demonstrated that visual sampling is task dependent and relates to specific goals
^26^. For example: during locomotion over even terrain, saccades may not be required. Over uneven (complex) terrain or during turning saccadic frequency, amplitude and fixations increase
^27–
30^. However many previous visual sampling protocols during dynamic task studies use small cohorts and often do not assess cognitive or visual functions
^15^, which limits interpretation and conclusions regarding underlying mechanisms. Visual sampling during gait therefore has not been fully investigated and further research is required to understand this important feature of gait control. Improved understanding will assist with interventions to improve gait performance in PD.

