***2) To examine the interaction between cognitive and visual functions (termed visuo-cognition)***

Visual sampling (saccade frequency) is an online behavioural measure of visuo-cognition due to its known relationship with cognitive and visual functions
^82^. To analyse visual sampling during gait, a series of mixed analysis of variance (ANOVA) will be used with effect of PD (PD and control) as between participant factor and attention (single task, dual task) and environment (Straight walk, Door, Turn) as within group factors. Pearson’s correlations will be used to test the strength and direction of the relationships between clinical, gait and saccade frequency outcomes. Gait characteristics will also be assessed with the same mixed ANOVA method.

To test the effect of visual cueing on visual sampling and gait; a mixed ANOVA will be used with group (PD and control), visual cue (no cue and cue) and attention (single task, dual task). Comparison with and without a visual cue will also be made via the same mixed ANOVA for the various gait characteristics, while controlling for the influence height.

Associations between cognitive and visual functions will be made using Pearson correlations. Cognitive and visual function contribution to visual sampling will be assessed using multiple regression analysis, while controlling for demographic factors (age, motor severity, depression, global cognition). This will be performed in several steps; Step 1: Demographics, Step 2: Cognition (attention, executive function, visuo-spatial ability, working memory), Step 3: Visual functions (visual acuity, contrast sensitivity), and Step 4: Visuo-cognition (combination of all of the variables in the above steps).

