## Discussion

The aims of this study were to provide a greater understanding of the roles that cognition and vision play in gait in PD. Specifically this study provided data regarding the role that visuo-cognition plays in gait in PD, as well as relationships between cognitive and visual functions (termed visuo-cognition). What sets this project apart from other work in this field is that the study is taking into consideration the combined and interactive impact that cognitive and visual function impairments have on gait in PD.

The study protocol was developed in response to recently reviewed evidence and study recommendations for visual sampling during a dynamic motor task
^15^. The protocol focussed not only on cognitive impairments but also visual dysfunction which is commonly reported in PD and until now has not been fully investigated. Little quantitative data has been previously reported regarding visual sampling during real-world tasks (e.g. gait, reaching etc.) in PD and the few previous studies available only involve small cohorts often performing simple static motor tasks (i.e. mouse clicks or button pressing or reaching
^92,
93^).

This study investigated the online visuo-cognitive behavioural measure of visual sampling during a real-world task (i.e. gait), and data analysis will examine interaction between visual sampling, cognitive and visual functions and task performance. The study will determine the influence of cognitive and visual functions on visual sampling during gait and gait characteristics in PD. This will allow us to determine whether gait impairments in PD are influenced by basic visual function (CS and VA) impairment or cognitive impairment (particularly attention) or a combination of these aspects.

Finally, an important feature of this study is that it is expected to provide the first evidence on the accuracy and reliability of using mobile eye-tracking equipment during gait with older adults and people with PD, which will develop the standard of research being conducted in this area and allow for more definitive conclusions.

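### The Step 2 regression increment adjusts cognition for the Step 1 covariates but not for vision, so it cannot be read as cognition's specific contribution to saccade frequency

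*Protocol article*

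**What the plan says.** Under Further analysis, aim 2, the protocol article states: "Cognitive and visual function contribution to visual sampling will be assessed using multiple regression analysis". The model is built "while controlling for demographic factors (age, motor severity, depression, global cognition"), which form Step 1. The next blocks are "Step 2: Cognition (attention, executive function, visuo-spatial ability, working memory), Step 3: Visual functions (visual acuity, contrast sensitivity"). The last is "Step 4: Visuo-cognition (combination of all of the variables in the above steps").

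The article does not say whether Steps 2 and 3 are cumulative or are separate models over Step 1. Nor does it say which step's statistic supports a statement about contribution.

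The question behind the regression is one of attribution. The Introduction names as poorly understood "the specific contribution of cognitive and/or visual functions to visual sampling during gait in PD". The Discussion promises: "The study will determine the influence of cognitive and visual functions on visual sampling during gait and gait characteristics in PD". It also expects to learn "whether gait impairments in PD are influenced by basic visual function (CS and VA) impairment or cognitive impairment", or a combination.

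**The concern.** A block's increment answers whether that block adds to what is already in the model. At Step 2 no visual measure is in the model. The null tested is that cognition is unrelated to saccade frequency given the Step 1 covariates. It is not that cognition adds nothing beyond vision. If the two functions remain correlated after Step 1, cognition can appear to contribute when only acuity and contrast sensitivity matter.

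The article gives reason to expect such a correlation. The Introduction says that "cognitive and visual functions likely interact and have a combined" impact on gait. The plan correlates the two sets of measures. Visuo-spatial ability, tested with visually presented material (clock copying, line orientation, incomplete letters), sits in the cognition block. At stake is a wrong statement about which function drives visual sampling.

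**Working it through.** The article states no R², power or error rate for this regression, so there is no figure to reproduce.

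**Inputs from the article.** Step 1 has 4 covariates, cognition 4 domains and vision 2 measures. There are 60 people with PD and 40 controls. The threshold is p<.05, two-sided. I take n=60 as the main case because motor severity is a covariate and Table 3 gives UPDRS part III for PD only.

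**Assumed inputs (none is in the article).** Correlations are 0.4 within cognition, 0.6 within vision and 0.2 within Step 1. The cognition-vision correlation r is 0.2 to 0.4. The correlation of Step 1 covariates with both blocks is 0 or 0.3. Only vision acts, explaining 20%, 30% or 40% of variance.

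**What each increment contains.** Write D, C, V for the Step 1, cognition and vision blocks.

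- Step 2 increment: R²(D+C) − R²(D)
- Cognition's unique part: R²(D+C+V) − R²(D+V)
- Shared part: the first minus the second

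So the Step 2 increment is cognition's unique part plus the shared part. The block test is F = [(R²_full − R²_reduced)/q] / [(1 − R²_full)/(n − k − 1)], where k is the number of predictors in the larger model. For Step 2, q=4 and the residual df are 60−8−1=51. For cognition entered last, q=4 and the df are 60−10−1=49.

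**Size of the shared part at r=0.4.** With equal correlations, the relevant quantity is the squared correlation between the sum of the cognition measures and the sum of the vision measures after Step 1.

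- *Covariates uncorrelated with both blocks.* Variance of the cognition sum: 4 + 12×0.4 = 8.8. Variance of the vision sum: 2 + 2×0.6 = 3.2. Covariance: 8×0.4 = 3.2. Share: 3.2²/(8.8×3.2) = 0.364. If vision explains 20% or 40%, Step 2 credits cognition with R² of 0.364×0.20 = 0.073 or 0.364×0.40 = 0.145.
- *Covariates correlated 0.3 with both blocks.* Step 1 removes 0.3²×4/(1+3×0.2) = 0.225 from every variance and covariance. The remaining cognition-vision correlation is (0.4−0.225)/(1−0.225) = 0.23. The variances become 4×0.775 + 12×0.175 = 5.2 and 2×0.775 + 2×0.375 = 2.3, and the covariance 8×0.175 = 1.4. Share: 1.4²/(5.2×2.3) = 0.164.
- *Same covariates, r=0.2.* The remaining covariance per pair is 0.2−0.225 = −0.025, so almost nothing is shared.

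**Simulated rejection for cognition, true cognition effect zero, n=60.** Ranges cover vision explaining 20% to 40% and are subject to simulation error.

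| Covariate-block correlation | r | Step 2 | Cognition last |
|---|---|---|---|
| 0.3 | 0.2 | about 5% | 4-6% |
| 0.3 | 0.3 | 5-8% | 4-6% |
| 0.3 | 0.4 | 12-23% | 4-6% |
| 0 | 0.2 | 10-16% | 4-6% |
| 0 | 0.3 | 18-36% | 4-6% |
| 0 | 0.4 | 31-63% | 4-6% |

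**Does the bias run one way?** This was checked with only cognition acting (partial R² 0.2), covariate-block correlation 0.3, within-vision correlation 0.5 and n=60. If the steps are cumulative, vision at Step 3 rejects in 5-6%. If Step 3 is a separate model without cognition, vision rejects in 24% (r=0.4) to 51% (r=0.5). So shared variance goes to cognition alone under the cumulative reading, and to each block in turn under the separate reading.

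**Power of the corrected test.** In the same cognition-only setting, the cognition block given vision is detected in 69% at r=0.4 and 52% at r=0.5, against 79% and 80% at Step 2.

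**The case against.** The strongest reply is that Step 4 contains every variable. A reader might infer from the step order that the two contributions cannot be told apart. The article does not support that: coefficients in the Step 4 model adjust cognition for vision and vision for cognition. In simulation a single cognition coefficient there rejects in 4.2-5.8% when cognition has no effect. What remains is that Step 4 is presented as the combination, not as a test of either block, and single coefficients are not a joint test of four correlated cognitive measures. If the steps are cumulative, Step 4 merely repeats the Step 3 model.

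Second, the article never says that conclusions rest on Step 2. That is true, and it limits the point to how the increment may be read. But the order is fixed in a plan that the article calls predetermined, and neither reading of it includes a block test of cognition given vision.

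Third, global cognition is in Step 1, and the MoCA covers several of the same domains, so adjustment may remove much of the overlap. This stands and is why the range starts at about 5%.

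Fourth, the study is exploratory, and aims 1 and 3 go to structural equation modelling with both functions. That lowers the weight. It does not repair the regression: the SEM drops indicators loading below 0.70, trims non-significant paths, and is aimed at gait.

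**Conclusion.** The concern holds in limited form. The Step 2 increment mixes cognition's own contribution with what it shares with vision and should not be reported as cognition's specific contribution. False credit at Step 2 ranges from about 5% to 31-63% over the assumptions tried, against 4-6% with cognition entered last. The deciding quantity, the cognition-vision correlation remaining after Step 1, is not in the article, so no single rate can be claimed.

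Two stronger readings are not supported. One is that false credit is necessarily well above 5%: with Step 1 covariates correlated 0.3 with both blocks, the excess vanishes at r=0.2 and is small at r=0.3. The other is that the bias always favours cognition, which is so only if the steps are cumulative.

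**What to change.** State whether Steps 2 and 3 are cumulative or separate. From the Step 4 model, report two block tests on equal footing: R² change and F for cognition added to Step 1 plus vision, and for vision added to Step 1 plus cognition. Report the shared remainder beside them. Base statements about each function's contribution on these tests, and keep the Step 2 increment as descriptive.

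No new data are needed, and the article still describes the analysis as to come. The cost is one extra run with the blocks reversed, a smaller reported R² change for cognition, and less power for the cognition block when the two functions are strongly correlated.

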## Aims

The aims of this study are to better understand: 1) the independent roles of cognition and vision in gait in PD, 2) the interaction between both functions (termed visuo-cognition), and 3) the role of visuo-cognition in gait in PD.

Secondary aims were to:

1.Investigate accuracy and reliability of mobile eye-tracking during gait in people with PD and older adults

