***3) To examine the role of visuo-cognition in gait in PD***

SEM will be used to assess an
*a priori* hypothesised model of visuo-cognition in gait in PD
^82^. This model will examine the inter-relationships between cognition, visual function, visual sampling (saccade frequency) and gait in PD. SEM is an ideal statistical method for assessing
*a priori* hypotheses, as it allows for hypothesised interactions between variables to be represented within the model. SEM combines ANOVA, correlation, path analysis, factor analysis and regression, and provides direct and indirect relationships between variables, which are not provided by regression analysis
^83^. Direct effects are those where a single path connects one variable to another. Indirect effects are those where the effect of one variable on another goes through a third variable (i.e. more than one path connects two variables)
^84^.

SEM analysis will be conducted using current industry recommendations
^85–
89^. Four steps will be undertaken:
1) Four latent variables will be created (i.e. cognition, visual function, visual sampling and gait) using the same observed variables (e.g. visual acuity) as within the multiple regression analysis.2) Poor latent variable representations will be removed (i.e. observed variables that do not meet a standardised factor loading of ≥0.70 will be removed for each latent variable
^89,
90^).3) Any observed variable with a standardised factor loading of ≥1.00 will be used in place of the latent variable to avoid overfitting
^89^.4) Model trimming and effect calculation; non-significant associations (connection arrows/paths) will be removed, and direct and indirect effects calculated (i.e. for indirect effects coefficients for each path will be multiplied
^91^).

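### Regression Step 4, labelled visuo-cognition, adds no term beyond Steps 1 to 3, and neither the regression nor the listed SEM steps name a cognition × visual-function term, although Aim 2 is stated as an interaction

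*Protocol article*

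**What the plan says.** The Aims section lists as its second aim "the interaction between both functions (termed visuo-cognition"), and the matching heading under Further analysis repeats it. The Conclusion says the study will give evidence on that interaction in PD.

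Under the Aim 2 heading, the plan for measured functions has two parts:

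- Bivariate: "Associations between cognitive and visual functions will be made using Pearson correlations".
- A stepwise multiple regression of visual sampling, "while controlling for demographic factors (age, motor severity, depression, global cognition"). These four variables form Step 1. Then come "Step 2: Cognition (attention, executive function, visuo-spatial ability, working memory") and "Step 3: Visual functions (visual acuity, contrast sensitivity"), and last "Step 4: Visuo-cognition (combination of all of the variables in the above steps").

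The same heading also plans mixed ANOVAs on saccade frequency and gait. One crosses group, attention (single or dual task) and environment (straight, door, turn). The other crosses group, visual cue and attention.

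Under Aim 3, the SEM has four latent variables: cognition, visual function, visual sampling and gait. The article recommends SEM because "it allows for hypothesised interactions between variables to be represented within the model". The four listed steps then cover creating the latent variables, screening on loadings, substituting observed for latent variables, trimming paths and multiplying path coefficients to obtain indirect effects.

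**The concern.** The step that carries the name visuo-cognition should be where the regression addresses the second aim. As defined, it brings in nothing that Steps 1 to 3 have not already named. An interaction in the statistical sense means that the effect of cognition on visual sampling differs by level of visual function. That needs a term for the pair, and none is named.

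What is at stake is interpretation. An R² from an additive model could be reported under the label visuo-cognition and read as evidence that the two functions interact, when it shows only that they jointly predict the outcome. The Discussion presents the study as distinctive because it considers an impact that is both combined and interactive. The additive model can support only the first of these.

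**Working it through.** The article gives no power, effect size or R² for this analysis, so there is no stated figure to reproduce. The check is a count of model terms, followed by the power of the proposed replacement.

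**Inputs from the article**
- Step 1: 4 variables (age, motor severity, depression, global cognition).
- Step 2: 4 cognitive domains.
- Step 3: 2 visual functions.
- Step 4: the same variables again, 0 new.
- PD group n=60; α = 0.05 two-sided.

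**Assumptions**
- Each domain enters as one score. Visuo-spatial ability is measured by several tests, so the true count could be higher.
- The regression is run in PD only, because motor severity is a covariate and Table 3 gives UPDRS part III for PD only.

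**Count of model degrees of freedom**

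| Reading | Step 1 | Step 2 | Step 3 | Step 4 | Step 4 − Step 3 |
|---|---|---|---|---|---|
| Hierarchical entry | 4 | 4+4 = 8 | 8+2 = 10 | 10 | 0 |
| Separate blocks, each with demographics | 4 | 8 | 4+2 = 6 | 10 | 4 |

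Under hierarchical entry the Step 3 and Step 4 design matrices span the same space, so the change in R² is exactly 0 for any data. A simulated data set with n=60 confirmed this: R² was 0.4519 at both steps. Under separate blocks Step 4 is a real model with 4 more df than Step 3, but all 10 terms are main effects.

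**Other analyses**
- A Pearson correlation between a cognitive and a visual score measures association. It does not measure whether one modifies the effect of the other.
- The listed SEM steps contain no cognition × visual-function latent variable. The only products are of path coefficients, which give mediation, not moderation.
- The factorial ANOVAs ordinarily estimate attention × environment, (2−1)(3−1) = 2 df; group × attention × environment, 2 df; and attention × cue, 1 df. These are interactions between imposed conditions and use no participant's cognitive or visual score.

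**Power of one product term in Step 4**

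Predictors 10+1 = 11; error df = 60−11−1 = 48. With main-effect R² assumed 0.30, f² = ΔR²/(1 − 0.30 − ΔR²). The test is a 1-df F test with noncentrality λ. Two conventions are in use: λ = f² × (1+48+1) = f² × 50, and λ = f² × 60.

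| ΔR² (assumed) | f² | Power, λ = 50f² | Power, λ = 60f² |
|---|---|---|---|
| 0.05 | 0.05/0.65 = 0.077 | 48% | 56% |
| 0.08 | 0.08/0.62 = 0.129 | 70% | 78% |
| 0.10 | 0.10/0.60 = 0.167 | 81% | 87% |

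Entering all 4 × 2 = 8 products instead gives 18 predictors and 41 error df. At f² = 0.15 (λ = 60f²), power is 84% for the single product and 45% for the 8-df test.

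**The case against.** A reader might infer that no interaction appears anywhere in the plan and that Aim 2 is never tested. The article does not support this. The section on measuring visual sampling during gait says that the environments vary visual complexity and the tasks vary cognitive demand. The ANOVAs therefore cross a cognitive load with a visual load, on saccade frequency, which the article treats as its online measure of visuo-cognition. That is experimental evidence bearing on a cognitive-by-visual interaction. It remains true that the plan does not name these terms as the Aim 2 test, and that they concern task conditions rather than participants' cognitive and visual functions.

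Three further points have force:

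- The article often uses interaction loosely, for relationship or combined influence. On that usage the correlations, the joint model and the SEM do address Aim 2, and part of the defect is terminology. But the Discussion speaks of impact that is combined and also interactive, so the stronger meaning is open to readers and needs either a test or a change of wording.
- Hierarchical entry is implied by numbered steps that control for demographics, but it is not stated. The zero change in R² holds only on that reading.
- The a priori SEM is in a cited source that is not shown. One cannot say that it has no interaction path, only that the listed steps name none. The remark that SEM can represent interactions describes the method and specifies no term.

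**Conclusion.** The point holds in this limited form and should be fixed. Step 4 is redundant under hierarchical entry (0 df, change in R² exactly 0) and purely additive under separate blocks. The regression and the SEM steps as listed name no term for measured cognition × measured visual function, so they cannot show that the effect of one depends on the other. The plan does not say which term tests Aim 2.

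This falls short of a fatal fault. The study is exploratory, the ANOVAs on the primary outcome are unaffected, and they already contain relevant interactions of task conditions. The structural conclusion rests on the article's own variable lists and needs no assumed figures. The power values do rest on assumptions: n=60 PD, one score per domain, main-effect R² of 0.30, and the choice of noncentrality. They describe what the fix can detect, not the size of the defect.

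**What to change.** 1. Redefine Step 4 as one pre-named, mean-centred product term added to Step 3. It could be a cognition composite × a visual-function composite, or attention × contrast sensitivity; the Discussion stresses attention and names contrast sensitivity as a basic visual function. State that entry is hierarchical.
2. Report the coefficient and the change in R² with 95% CIs, as exploratory.
3. Name attention × environment and attention × cue in the mixed ANOVAs as the experimental test of Aim 2.
4. Describe the additive model as a combined contribution, not an interaction, there and in the Conclusion.

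Cost: a few sentences and 1 model df; all variables are already collected. The drawback is limited power. Only a fairly large interaction is detectable at n=60, so a non-significant product must not be read as absence of interaction. Keeping to a single product matters, because the 8-product version loses much of the power.
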